## Abstract

**Background:**

Health-promoting actions might benefit from adolescent health literacy (AHL), however, there is scant research on it in Nepal. This study identifies adolescent students’ health literacy (HL) needs and trials an intervention to improve their HL and intention to take health-promoting actions.

**Methods:**

This study employs a pre-and post-test mixed-method intervention involving three phases. First, we will conduct a formative and summative evaluation to identify participants’ HL needs and design an intervention using quantitative and qualitative methods. Second, the intervention will be administered to the intervention group. Finally, formative and summative post-tests will be conducted to assess the effectiveness of the intervention. We will select four community schools from Birendranagar municipality based on random sampling. In quantitative research, data will be collected from adolescents selected through a census with standardized scales such as the HLS-Child-Q15, self-efficacy, social support, and health-promoting actions. A framework analysis was conducted to analyze qualitative data collected from focus group discussions with purposively chosen adolescents and key informant interviews with Health and Physical Education teachers and school nurses. The *difference in difference* approach will be used to analyze the intervention’s outcome, i.e., the participants’ improved HL, and health-promoting actions.

**Discussion:**

This is one of the first studies to explore HL in this group in Nepal. This study will provide the first insights into the overall level of AHL, potential AHL determinants, and the relationship between AHL and the intention to participate in health-promoting activities. The data can then be used to inform health promotion and health literacy initiatives.

## Background

HL is a relatively new research field and an essential part of public health [1–4] and health promotion [5, 6]. Schools can play an influential role in promoting HL [7] by delivering health information through mandatory courses on health education to all school-aged children [8]. This makes HL a viable target for schools. Health education and promotion make a significant contribution to HL [5] and could be considered as a part of the Health Promoting School (HPS) [9, 10]. The growing interest in adolescent health literacy  (AHL) in recent years has been discussed worldwide [9]. Moreover, it has been argued that AHL research is crucial [11], but received far less attention than research on adults’ HL in many contexts [9].

The understanding of AHL is limited due to a paucity of studies [9, 12, 13], particularly in developing countries [14]. Evidence shows that low AHL is common even in developed nations [15–17]. For example, the majority of school-going students (67.2%) in ten European countries have only a moderate level of HL [18, 19]. Studies show that the HL of school-aged children is low. According to a study on Thai school-aged children, 64.4% reported poor levels of HL [20], followed by one-third for Chinese children [21]; 20.9% of Pakistani children had very limited, and 53.4% limited HL [22] and almost (99.3%) of Iranian students from 15 to 18 had poor HL [23]. Only a few HL studies have been conducted in Nepal, revealing that the majority of female college students [24, 25] and school adolescents have inadequate HL scores [26]. These studies provide the first insights into AHL, but the overall distribution of AHL remains unclear [21] and differs among countries and subgroups [18]. As per our current understanding, not much is known about the distribution of AHL in the population [27].

The next issue is that there is currently a scarcity of theory-driven HL interventions in schools to increase AHL. A limited number of studies have been conducted to develop interventions to promote generic HL in adolescents. For example, a recent review found that no intervention has explicitly aimed to improve HL [28] and the majority of existing school-based HL interventions are domain-specific without a holistic model [29]. It is frequently ignored in school curricula [30] and an effective strategy for improving HL in schools is still lacking [31]. Further, the literature shows that most of the studies conducted on the HL of adolescents are cross-sectional designs. To our knowledge, this will be the first intervention study to promote health literacy among adolescent school students in Nepal. This is why a longitudinal research design is employed in this study.

## Aims

Based on the available evidence, this study aims to.

(i)explore the HL needs of adolescent students and.(ii)design, implement and evaluate the impact of a health literacy educational intervention to improve adolescent students’ health literacy and their intention to take health-promoting actions.

## Methods

### Research method

The study follows a pre-and post-test [32, 33], mixed-method intervention design [34] grounded in pragmatism. Researchers have identified pragmatic research as the preferred approach to mixed-methods research [32, 33, 35, 36].

### Theoretical model

While reviewing the various models [37–39] in light of this study’s overall goals, the comprehensive and conceptual model appears to be applicable as a theoretical model [40]. The understanding of HL within this study is underpinned by the four core dimensions of the HL Model as presented by Sorensen et al. (2012): (1) accessing, (2) understanding, (3) appraising, and (4) applying health information. Based on this model, this study will explore the multiple determinants that shape HL (Fig. 1), namely (1) personal, (2) situational, as well as (3) societal and environmental determinants. All three factors influence how adolescents deal with health information. Also, the model covers many potential outcomes of HL. Of these outcomes, the study will cover only health-promoting actions as a specific form of health behaviors [6].

**Fig. 1 Fig1:**
[figure not shown]
Simplified HLS-EU model of health literacy [40] adapted to the study design and needs

### Study site

This study will be conducted in the governmental school of Birendranagar Municipality of Surkhet. There are a total of 21 schools in the municipality where 2500 (average: 156 per school) students are studying in class nine in this academic session [41]. Karnali Province is less developed, has low human development indicators, and has a low literacy rate compared to other provinces of Nepal [42, 43]. Birendranagar is an educational and cultural hub where students from different districts of Karnali province come to study. Therefore, it has been selected as a study area.

### Research design

This study contains three phases (see Fig. 2). Formative and summative evaluation will be used to explore the impact of the intervention. Formative assessment will assess the feasibility and acceptability of interventions and help inform their implementation [34]. Summative evaluation will be used to investigate the impact of the intervention.

**Fig. 2 Fig2:**
[figure not shown]
Overview of the research design

### Phase 1 needs assessment

As part of the formative evaluation [34], all class nine students, as well as their Health and Physical Education (HPE) teachers and school nurses from the four schools will take part in quantitative and qualitative pre-tests. This phase will assess participants’ HL knowledge, and, needs. This phase [44] will also inform the implementation strategies [34, 45].

The HL Intervention will be developed in three steps. First, the researchers will prepare a preliminary draft of the intervention based on the IM’s four dimensions (accessing, understanding, appraising, and applying health information [40]), and the HPE curriculum of class nine. Second, the preliminary draft will be refined based on the HL needs of the target group. This will then be further refined by the Delphi study with HPE teachers, school nurse, health education, public health and medical care experts. As part of this process, the 9th -grade HPE curriculum will be integrated into the interventions’ contents, strategies, materials, and practical facilitation of the sessions. Third, to make it more aligned with HL needs, the curriculum, and the HL domains (accessing, understanding, evaluating, and applying), the refined draft will be finalized based on consultation with health educators and health literacy experts (see Fig. 3).

**Fig. 3 Fig3:**
[figure not shown]
Flow chart of the intervention development process

### Phase 2 implementation

In this phase, the refined intervention will be implemented in the intervention group in eight separate classroom sessions. One session will last for 1 h to 90 min. Teachers from participating schools, HPE teachers from participating local campuses, public health officers, and medical officers will conduct the sessions (Table 1).

**Table 1 Tab1:** Preliminary intervention draft based on IMHL [40] and HPE curriculum

Input	Sessions	Objectives	Contents	Activities	Outcome
Program introduction	Researcher	To become familiar with the program	Introduction to program, and HL and health-promoting actions	Group teaching and interaction	Increased HL awareness and skills Intention to engage in health promotion actions
Human resources Time Money Materials Technology Partnership	Health education experts	to raise adolescents’ awareness of health literacy.	Health Literacy (HL) concept	Storytelling and Dialogue	
	HPE teacher/ school nurse	To develop Confidence in health literacy skills	Health information: access, understand, appraisal, and apply	Clear communication, photograph showing demonstration, experience sharing	
	Teacher’s educator	Confident to evaluate the determinants of health	Social determinants of health, health right, and responsibility	Video showing and Dialogue	
	Medical doctors	Confident to use health care	Health care literacy	Clear communication, role playing	
	School Nurse	To raise awareness on disease prevention	Disease prevention literacy	Experience sharing, playing game	
	Public health experts	To raise awareness on disease prevention	Health promotion literacy	self-assessment and reflection of text and presentation	
	Health education experts	to pursue health-promoting activities	Health-promoting actions	Case study, video show, playing game, group discussion	

### Phase 3 evaluation

Both formative and summative evaluation methods will be employed to evaluate the impact of the health literacy educational intervention. Based on the above description, pre-interventional evaluation [34] information will be collected from students, HPE teachers, and nurses through quantitative and qualitative pre-tests, as well as a review of the grade nine curriculum. Discussion and meetings will be conducted with HPE teachers, students, and facilitators during the implementation process. This is to determine whether the plan is being implemented properly and whether there are any discrepancies [46].

To evaluate the overall success, usefulness, satisfaction, and additional suggestions [34], contextual appropriateness, relevancy, and acceptability [44] of the intervention, interpretative formative evaluation [46] will be used. Summative evaluation will be used to assess the overall effectiveness of the intervention at the end of the project.

### Participants and sampling

The study will involve adolescent students in grade nine as primary participants, and HPE teachers and school nurses as secondary participants. Since academic grades and age affect HL, only grade nine will be taken for this study to construct the same group of intervention and control [39].

#### Sampling for a quantitative study

Firstly, four governmental secondary schools will be chosen from the study area using a random sampling method for the needs assessment. Then, two of the four selected schools will be considered as an intervention group randomly and the remaining two schools will be considered as a control group. The sample size of this study will be at least 384. All students of class nine of the selected schools will be selected via the census. Assuming that the margin of error is 5% and the level of confidence is 95%, the recommended standard sample size (SSS) is 384 [47]. Non-response samples will be added after the pilot test.

The formula of SSS [47]: $$n={\text{z}}^{2}\left(p\right)\left(q\right)/\left(e\right)$$[where n= sample size, Z= standard error associated with the chosen level of confidence, p= variability/, q = 1-p, and e= acceptable sample error] will be used.

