### Data analysis procedure

For the formative assessment of HL needs, quantitative data will be analyzed by descriptive analysis. The software SPSS version 20.0 will be used to conduct all statistical analyses for quantitative data. Ritchie & Spencer’s (1994) five- steps framework analysis [57] will be applied to analyze the qualitative data from the pre-and post-tests. The verbatim recordings will be transcribed and ATLAS-TI software will be used for coding and categorization.

The summative evaluation methods will be used to compare pre-test and post-test results to determine if there has been any change in response. The Different in Different (DID) method will be applied to measure the impact of the program [58] which is also known as the double-difference method. Differences in the outcomes before and after intervention in both groups will be analyzed [45]. Mean, standard errors, mean differences, and a comparison of the results between the pretest and posttest will be examined.

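### The 384 is a simple-random-sample figure for one proportion; a census of four schools delivers its 5% margin only if the ICC is essentially zero, and it gives no basis for the DID comparison

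*Protocol article*

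**What the plan says.** The sample size is set under 'Sampling for a quantitative study' in the protocol article. "The sample size of this study will be at least 384", and the reason given is "Assuming that the margin of error is 5% and the level of confidence is 95%, the recommended standard sample size (SSS) is 384". The formula is z²·p·q divided by e, with "p= variability/, q = 1-p, and e= acceptable sample error". No value of p is printed.

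The same section describes how students enter the study:
- On the draw of schools: "four governmental secondary schools will be chosen from the study area using a random sampling method for the needs assessment".
- On allocation: "two of the four selected schools will be considered as an intervention group randomly and the remaining two schools will be considered as a control".
- On selection within schools: "All students of class nine of the selected schools will be selected via the census".
- On losses: "Non-response samples will be added after the pilot test".

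Under 'Data analysis procedure', the DID "method will be applied to measure the impact of the program". No other basis for the sample size appears in the article.

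**The concern.** The stated margin belongs to a design in which 384 students are drawn independently. Here the schools are drawn, and each brings its whole class nine. Students in one school tend to resemble each other, and a census within the school does nothing about variation between schools. An estimate for the municipality therefore rests largely on four school means.

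The second aim of the study is to evaluate an intervention by comparing changes between two pairs of schools. The formula contains no effect size, SD, power, pre-post correlation or arm, so its result carries no information about that comparison.

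This is the only precision figure in the article, and it is called the sample size of the study as a whole. If it stands, the needs-assessment estimates could be reported with a precision they do not have, and the number could be cited in support of a comparison it was never calculated for.

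**Working it through.** **Inputs from the article.** e = 0.05, 95% confidence (z = 1.96), total at least 384, 4 schools of 21, two schools per arm. 'Data collection procedure' speaks of three remaining control schools; I use two, as in the sampling section, because four less two is two. Students per school, m:
- 384/4 = 96, the stated minimum;
- 2500/21 = 119, from the totals under 'Study site';
- 156, the average printed there.

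**Inputs assumed.** ICC 0.01, 0.02, 0.05; pre-post correlation r of 0.3, 0.5, 0.7, taken as equal at student and school level; 80% power; two-sided 5% test. The article gives none of these.

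**1. The stated figure.** With p = 0.5, the value that yields 384:
- 1.96² × 0.5 × 0.5 / 0.05² = 384.16. This reproduces 384.
- As printed, 1.96² × 0.5 × 0.5 / 0.05 = 19.2. So e² was used and e was printed.

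**2. Margin with whole schools.** Design effect DE = 1 + (m − 1)·ICC; margin = 1.96·√(0.25·DE/N), with N = 4m.

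| ICC | DE, m = 96 | Margin, N = 384 | Margin, N = 476 (m = 119) | Margin, N = 624 (m = 156) |
|---|---|---|---|---|
| 0.01 | 1.95 | 7.0 | 6.6 | 6.3 |
| 0.02 | 2.90 | 8.5 | 8.2 | 7.9 |
| 0.05 | 5.75 | 12.0 | 11.8 | 11.6 |

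Margins are in percentage points. Worked example: 1.96·√(0.25 × 1.95/384) = 0.070.

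These use the normal approximation. With only four schools, t on 3 df (3.182) gives 11.3, 13.8 and 19.5 points at N = 384.

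**3. Largest ICC compatible with 5 points.** Set N = 384.16·DE and solve:
- m = 96: zero;
- m = 119: (476/384.16 − 1)/118 = 0.002;
- m = 156: (624/384.16 − 1)/155 = 0.004.

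**4. Finite-population correction for 4 of 21 schools.** √((21 − 4)/(21 − 1)) = 0.922. At N = 384 the margins become 6.4, 7.9 and 11.1 points. The limits in step 3 move to about 0.002, 0.004 and 0.006.

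**5. Two-arm comparison.** In SD units a school mean has variance DE/m. With two schools per arm, the difference between arms at one time point has variance DE/m. For the DID the standard error is √(DE/m)·√(2(1 − r)). Four schools less two arms leave 2 df, and 80% power then needs a noncentrality of 5.65. Detectable DID = 5.65·√(DE/96)·√(2(1 − r)):

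| ICC | r = 0.3 | r = 0.5 | r = 0.7 |
|---|---|---|---|
| 0.01 | 0.95 | 0.81 | 0.62 |
| 0.02 | 1.16 | 0.98 | 0.76 |
| 0.05 | 1.64 | 1.38 | 1.07 |

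Treating 192 students per arm as independent, at r = 0.5, would give 2.80·√(2/192) = 0.29 SD. At m = 156 and r = 0.5 the 2-df values are 0.72, 0.92 and 1.34 SD, so larger schools change little.

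**The case against.** The best defence has four parts.

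*384 is a floor.* A census of average-sized schools would bring in about 476 to 624 students. That stands, and the larger sizes are shown above. They lower the margin by less than one point at each assumed ICC, because the number of schools dominates.

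*The ICC is not in the document.* That also stands. A reader might infer that 384 is inadequate for both purposes whatever the data look like. The article does not support that: with 119 or 156 per school the 5% margin survives an ICC up to about 0.002 or 0.004 by the normal formula. Nor is there sampling error if the needs assessment serves only to tailor the intervention to these four schools. The point bites when results are generalised, which the abstract hopes to do.

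*No power is claimed.* Correct. The discussion promises only preliminary evidence and concedes imperfect randomisation. A power calculation may sit in a fuller document, and its absence here is not the complaint. What can be faulted is the reason the article does print.

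*The non-response sentence is workable.* A reader might infer that it is impossible, since a complete census leaves nobody to add. But the pilot uses students outside the study, so the sentence can mean raising the planning target beforehand. It is unclear rather than wrong.

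**Conclusion.** The stated justification is wrong for the design in the same section. The figure of 384 is the simple-random-sample size for one proportion, printed with a formula that does not produce it. In four intact schools the 5% margin requires an ICC of practically zero. At ICCs of 0.01 to 0.05 the margin is about 6 to 12 points across the plausible enrolments, with or without a finite-population correction.

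The figure is no basis for the DID. On school-level inference with 96 per school, the detectable effect runs from 0.62 SD (ICC 0.01, r = 0.7) to 1.64 SD (ICC 0.05, r = 0.3). These sizes rest on assumed ICCs and correlations, and a higher pre-post correlation would lower them. That the formula does not fit the design, and has no link to the comparison, depends on none of these assumptions.

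A reader might go on to conclude that the trial is shown to be underpowered. The article names no target effect, so that cannot be said.

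**What to change.** Reword the sample-size paragraph, without enrolling more:

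1. Print the formula with e² and state p = 0.5.
2. Remove the claim that the design gives a 5% margin.
3. State the expected class-nine enrolment of the four schools, with two schools per arm.
4. Give the cluster-adjusted margin for the needs assessment over a stated range of ICCs, and say to which population it applies.
5. Give the minimum detectable DID on 2 df over stated ranges of ICC and pre-post correlation.

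Optionally, say that the non-response allowance raises the planning target, because a census of fixed schools cannot be topped up later.

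The cost is one paragraph and a less favourable stated precision. The rewording does not remove the underlying limit, which is two schools per arm, but it makes that limit visible.

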#### Sampling for a qualitative study

Twenty-four (six from each school) adolescents will be purposefully selected from the participating schools. Similarly, HPE teachers and school nurses of the respective schools will also be included as key informants for the study.

### Inclusion and exclusion criteria

All students in class nine of selected schools in Surkhet, aged 13 to 19, who are willing to participate in the study, will be included. However, students with special needs and who skip two educational sessions will be excluded from the intervention.

### Tools and materials

#### Quantitative data collection tools

Information about participants’ characteristics such as age, sex, caste, religion, parental education, family size, availability of TV, radio, mobile, internet, health status, educational outcome, and HL knowledge will be collected using a self-administered questionnaire. To collect quantitative data relating to the pre-test and post-test, standardized tools will be used, such as self-efficacy, social support, school environment, community environment, HLS CHILD-15, and health-promoting action scale (Table 2).

**Table 2 Tab2:** *Standardized data collection tools*

SN	Variable	Tools	Literature	Total items and components	Reliability	Validity
1	Personal factors	General Self-efficacy Scale (GSE)	R Schwarzer and M Jerusalem [48]	10 items 4 scales, ranges between 10 and 40	α = 76 to 0.90	Strong structural validity
2	Situational factors:	Multi-dimensional scale for perceived social support Scale (MSPSS)	GD Zimet, NW Dahlem, SG Zimet and GK Farley [49]	12-item scale family (4), friends (4), significant other (4).	α = 0.86–0.93)	good construct validity
3	School Environment	The school environment scale (SES)	R Glaser, ML Van Horn, M Arthur, J Hawkins and R Catalano [50]	17 items: chances for pro-social participation (5), rewards for pro-social involvement (4), academic performance (2), commitment to school (6)	α = 0.70–0.76)	Strong construct validity
4	Community Environment	The community environment scale (CES)	M Gray and A Sanson [51]	Nine items related to a neighborhood environment	α = 0.84	Satisfactory construct validity
5	Subjective health literacy	HLS-CHILD-Q15	TM Bollweg, O Okan, P Pinheiro, J Bröder, D Bruland, AM Freţian, OM Domanska, S Jordan and U Bauer [52]	15-items, access, understand, and apply	α = 0.71 to 0.74	Significant
6.	Assessing health-promoting actions	Health-promoting actions questionnaire (HPAQ)	SN Walker, KR Sechrist and NJ Pender [53]	6 aspects; Self-actualization, health responsibility, nutrition, interpersonal support stress management, and exercise.	0.92 and	Significant

